## Abstract

**Background:**

Patient-reported outcome measures provide an essential perspective on the quality of health care provided. However, how data are collected, how providers value and make sense of the data, and, ultimately, use the data to create meaningful impact all influence the success of using patient-reported outcomes.

**Objectives:**

The primary objective is to assess post-operative pain experiences by dental procedure type through 21 days post-procedure as reported by patients following dental procedures and assess patients’ satisfaction with pain management following dental surgical procedures. Secondary objectives are to: 1) assess post-operative pain management strategies 1 week following dental surgical procedures, as recommended by practitioners and reported by patients, and 2) evaluate practitioner and patient acceptance of the FollowApp.Care post visit patient monitoring technology (FollowApp.Care). We will evaluate FollowApp.Care usage, perceived usefulness, ease of use, and impact on clinical workload.

**Design and methods:**

We describe the protocol for an observational study involving the use of the FollowApp.Care platform, an innovative mobile application that collects dental patients’ assessments of their post-operative symptoms (e.g., pain). The study will be conducted in collaboration with the National Dental Practice-based Research Network, a collective Network of dental practices that include private and group practices, public health clinics, community health centers and Federal Qualified Health Centers, academic institutional settings, and special patient populations. We will recruit a minimum of 150 and up to 215 dental providers and up to 3147 patients who will receive push notifications through text messages FollowApp.Care on their mobile phones at designated time intervals following dental procedures. This innovative approach of implementing an existing and tested mobile health system technology into the real-world dental office setting will actively track pain and other complications following dental procedures. Through patients’ use of their mobile phones, we expect to promptly and precisely identify specific pain levels and other issues after surgical dental procedures.

The study’s primary outcome will be the patients’ reported pain experiences. Secondary outcomes include pain management strategies and medications implemented by the patient and provider and perceptions of usefulness and ease of use by patients and providers.

**Supplementary Information:**

The online version contains supplementary material available at 10.1186/s12903-022-02573-9.

Contributions to the literature
Patient self-report is a critical part of comprehensive pain assessment. By promptly collecting patient health assessments, we will offer practitioners an opportunity to assess the effectiveness of their treatment modalities to understand their patients’ experiences and health outcomes.In this study, dental practitioners can respond in real-time to patient-reported outcomes for post-operative pain management.Evidence suggests that mobile phones are an effective platform for assessing patients’ symptoms and symptom burden. In addition, mobile applications can be effective in collecting and utilizing patient-reported outcomes to tailor care, however, they are rarely used in dentistry.Knowledge of treatment recommendations and/or patient reports will provide useful information in the shaping of dental school curricula.

## Background

Existing means to address unexpected post-operative discomfort following a dental procedure include preemptively prescribing pain medication that might not be needed or having the patient call/visit the dental clinic before the regularly scheduled follow-up time period. Both approaches do not reflect patient-centered care and carry the risk of under/ overprescribing analgesics - including opioids. As the PEARL network concluded in its 2015 study examining dentists’ post-procedural prescriptions, “dentists tended to expect more pain than patients actually experienced; however, the choice of medication prescribed or recommended did not reflect the dentists’ expectations or the patients’ outcomes [1].” Oral health providers’ inability to monitor post-operative pain in real-time, and their desire to prevent unwanted, unscheduled visits, have driven them to heavily prescribe opioids in a failed attempt to satisfy patients’ short-term pain management [2–4].

Patient-reported outcomes (PROs) provide an essential perspective on the quality of health care and facilitate clinical decision-making. Electronic and paper-based administration of PROs has proven to be equally effective [5]. Data collection procedures, along with how providers value and make sense of the data and, ultimately, use it to create meaningful impact, all influence the success of using PROs [6]. PROs are widely used to inform individual care and manage the performance of healthcare [7]. However, assessing PROs in real-time as part of out-patient care is challenging. Studies on the use of PROs in medical health systems show that PROs must be easy (simple user-interface, convenient timing), fast (short questionnaire length and frequency), and relevant (inform clinical care). For providers, PROs should make care easier (reduce administrative burden), faster/better (improve quality of visit), and relevant (solve discipline-specific problems) [8]. Unfortunately, the use of PROs in dentistry is not widespread, thereby limiting the ability of dental providers to respond in real-time to post-operative pain management by unlocking the power of PROs.

Current applications of Health Information Technologies (HIT) in dentistry are limited to electronic health records (EHRs) in general [9, 10], using EHRs for non-clinical management purposes [10–13], and unconnected “gadgets”, such as CAD/CAM systems, intraoral cameras or ConeBeam CTs. However, growing evidence from our medical colleagues suggests that mobile phones are an effective platform for assessing patients’ symptoms, symptom burden, health status, health behaviors, and health-related quality of life [14–19]. For example, a study by Stein et al. explored the feasibility of using smartphone applications to triage dental emergencies [20]. Another study from the UK revealed that mobile applications motivated dental patients to maintain better oral hygiene [21]. With 85% of US adults owning a cellphone [22], and 67% of patients using their phones to search for health information [23], dental providers need to embrace HIT as a strategy for delivering quality care to improve the oral health their patients. This is especially important when interacting with low SES families as a significant proportion of them only connect to the Internet via smartphones [24].

While research on the effectiveness of text messages and mobile app-related inventions to improve the quality of care is still in its infancy, results from studies using other forms of HIT are promising. For instance, mPOWEr enables patients to provide feedback on the condition of their surgical incision site following discharge from the hospital, while other mobile apps that collect PRO data enable patients to monitor their chronic health conditions, such as diabetes [25, 26]. Additionally, participants in a chemotherapy treatment group using a web-based PRO questionnaire platform to report their symptoms had fewer hospitalizations, emergency room visits, and overall higher survival rates [27, 28]. Results of studies like these indicate that mobile apps could effectively collect and utilize PROs to tailor care [29], particularly in dentistry, where HIT is rarely used to collect PROs.

In our pilot study (AHRQ 1U18HS026135), we successfully explored how an innovative mobile health intervention (FollowApp.Care®) could optimize the quality of acute post-op dental pain management by collecting PRO data from patients after dental procedures. However, it also taught us a number of implementation barriers. Some of these barriers are not new to those collecting PRO data, including difficulties with optimizing workflows and minimizing logistical burdens, further exacerbated by the expanded precautionary settings during COVID; data management in light of staff turnover; and staff training and providers [30, 31]. Barriers specific to implementing dental PROs using mHealth included making sure that providers see and act upon alerts timely; a hybrid approach to recruitment of patients due to the COVID environment; inaccurate phone numbers, and phone carrier contractual issues that prevented text messaging.

These barriers can substantially hamper the implementation of PROs by the general dentist, to the detriment of advancing patient-centered care in the dental arena. In the POPS (**P**ost-**O**perative **P**ain **S**tudy) trial (UH3DE029158, Understanding Pain after Dental Procedures), we seek to address the gap in knowledge by implementing an existing mHealth technology (FollowApp.Care) in the dental office setting. Through the FollowApp.Care platform, we will actively track pain and other complications following dental procedures. We expect to identify specific pain experiences associated with surgical dental procedures promptly and precisely. We will also collect information about pain management strategies and medications recommended by the practitioner and utilized by the patient. The results of this study will provide insight into pain and other postoperative complications experienced by patients through approximately 3 weeks following common dental procedures. We will also be able to gauge to what extent practitioners are interested in adopting mHealth technology. We will also learn how patients like to be engaged with text messaging to report post-operative pain and complications.

## Objectives

### Primary objective is

To assess post-operative pain experiences by dental procedure type through 21 days post-procedure as reported by patients following study-eligible dental procedures and assess patients’ satisfaction with pain management following dental surgical procedures.

### Secondary objectives are

Assess post-operative pain management strategies at 1 week following dental surgical procedures, as recommended by practitioners, and reported by patients.Evaluate practitioner and patient acceptance of FollowApp.Care. We will evaluate FollowApp.Care usage, perceived usefulness, ease of use, and impact on clinical workload.

## Hypotheses

The study includes the following hypotheses:

### Hypothesis 1

There is a significant difference in pain intensity measured over time and the dental procedure groupings after adjusting for pain management strategies and other complications. More specifically, are their significant variations in pain intensity due to different treatments after adjusting for:pain management strategy (e.g., pain medications used, adherence to pain management strategy, the usage of non-medicine methods for pain)other complications

### Hypothesis 2

There is a significant difference in pain interference measured over time and the dental procedure groupings, after adjusting for pain management strategies and other complications. More specifically, are their significant variations in pain interference due to different treatments after adjusting for:pain management strategy (e.g., pain medications used, adherence to pain management strategy, the usage of non-medicine methods for pain)other complications

### Hypothesis 3

There is a significant difference in patient satisfaction measured at the end of the 7-day period and dental procedure groupings, after adjusting for pain management strategies and other complications. More specifically, are their significant variations in patient satisfaction due to different treatments after adjusting for:pain management strategy (e.g., pain medications used, adherence to pain management strategy, the usage of non-medicine methods for pain)other complications.

### Hypothesis 4

Reported technology acceptance metrics; performance expectancy (PE), effort expectancy (EE), social influence (SI), and behavioral intention (BI) will be consistent with high acceptance of the FollowApp.Care platform.

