Secondary outcomes include 1) *Analgesic medications used by patients* that are reported through FollowApp.Care, frequency and dose prescribed captured through the eCRF completed by the practitioners; adherence to pain medications prescribed collected from the patient-reported data through FollowApp.Care, 2) *Concordance with pain management strategy* as recommended by the practitioner (reported on the eCRF) and reported by the patient. The pain management strategy of each practitioner will be captured on the eCRF, and the mHealth questionnaire will capture the corresponding patient adherence. 3) *Other pain management strategies* used by patients (post-op pain management strategies including usage of other pain management strategies, such as non-medicine methods for pain relief), 4) *Practitioner acceptance* of the platform (usage, perceived usefulness, ease of use, and impact on clinical workload), 5) *Patient perceived usability* with the platform (usefulness and ease of use of the platform), and 6) *Other complications* related to immediate postoperative complications (bleeding and increased swelling).

Other covariates are *Baseline pain intensity, Patient demographic* variables, *Type of procedure* (CDT), P*ractitioner demographic* variables, *Practitioner specialty, Practitioner years in practice (*the year of graduation from dental school), and Practitioner assessment of *expected pain intensity.*

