*Practitioner acceptance* with the FollowApp.Care platform will be measured by the Unified Theory of Acceptance and Use of Technology (UTAUT) [47] questionnaire to evaluate FollowApp.Care usage, perceived usefulness, ease of use, and impact on clinical workload. The UTAUT model measures the relationships between use intention and two independent constructs – performance expectancy and effort expectancy. The UTAUT model integrates eight major theories and has been tested and validated using large real-world data sets (see Additional file 3: Appendix 3).4.electronic Case Report Form (eCRF)

Two eCRFs record practitioner information (practitioner characteristics) and patient information (patient demographics, diagnoses and procedures, pain levels, pain management plan, and complications) at Days 0 & 21 (see also Appendix 3).5.Debriefing/interview

Telephone debriefing/interviews with purposefully selected practitioners will be conducted to qualitatively evaluate their experiences with using FollowApp.Care for managing their patients’ post-operative pain, including its impact on their clinic workload and workflow patterns, and satisfaction with the effectiveness of pain management.

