UTAUT Questionnaire	After practitioner completes enrollment of all their patients	Explores four core constructs: performance expectancy, effort expectancy, social influence, and facilitating conditions as direct determinants of behavioral intention and behavior	Practitioners
electronic Case Report Form (eCRF)	Days 0 and 21	Two eCRFs: - Practitioner info (practitioner characteristics) - Patient info (diagnoses and procedures, pain levels, pain management plan, and complications)	Practitioners
Debriefing/interview	After practitioner completes enrollment of all their patients	Practitioners’ experiences with using FollowApp.Care for managing their patients’ post-op pain.	Practitioners

Patients will also be asked to evaluate the usability of the FollowApp.Care system by completing the 10-item, System Usability Scale survey and providers the UTAUT questionnaire. Once the patient component of the study has been concluded, we will conduct telephone interviews with providers to qualitatively evaluate their experiences with using FollowApp.Care for managing their patients’ post-operative pain, including its impact on their clinic workload, workflow patterns, and satisfaction with the effectiveness of pain management.

See Table 3 for an overview of study activities.

**Table 3 Tab3:** Study activities

Task	Description of implementation/operationalization
1. Network Site Selection	We anticipate that all Network practitioners stratified by state, urban/rural, and practice size, will be eligible to participate. We will work with the Network coordinators to assure all sites are informed of the study protocol and the opportunity to participate.
2. Practitioner Recruitment and training	The Network site coordinators will use established protocols to recruit practitioners. The study team will work with the coordinators and the Network Communications Director to assure the dissemination of the study opportunity. The study team will provide the coordinators with all online training materials. Coordinators may decide to add an in-person training component. Study personnel will be available remotely via video conference/phone calls to support all training efforts.

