### Statistical analysis

Standard descriptive statistics will be used to describe both patient and practitioners’ characteristics using 5 data capture methods: 1) the SUS questionnaire, 2) the mHealth Questionnaire distributed on pre-specified days post procedure, 3) the UTAUT questionnaire, 4) the debriefing/interviews, 5) and the practitioner eCRF. Summary statistics such as means, medians, and ranges will be produced for all measured continuous variables. Frequencies and percent contributions will be computed for all categorical and ordinal variables. Graphical methods like X-charts will examine distributions over time and identify potential, influential time points. The balance of baseline characteristics and measures between groups will be compared using appropriate tests, including chi-squared tests, student t-tests, and Wilcoxon rank-sum tests.

A challenge for this non-randomized study is confounders – pre-existing variables that affect the outcomes and differ between the treatment groups. In order to reduce bias, potential confounders variables will be adjusted in regression models for the analysis. Once participants discontinue the study, they will not be contacted and will not be replaced as the power calculation has accounted for them. If the discontinuation rate is high, the study team PIs will discuss how to proceed with the Network and NIDCR. We will create a missing category for all missing data and assess the need for any imputation methods.

We will estimate the difference in intensity, pain interference, and patient satisfaction dependent on the treatment type. The relative risk (RR) will be the measure of association reported along with 95% confidence intervals. Pain, interference, and satisfaction at the end of the study will be compared among the treatment categories. To model the differential treatment (CDT Grouping) effect on patients’ pain intensity, interference, and satisfaction, on, we will use GLMMs using a Poisson link. Models will include time, treatment type, age, gender, race/ethnicity, medications, and no medication methods as fixed effects. In addition, dentist and Network regions will be included as random effects in the models to account for correlations within clusters.

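### Hypotheses 1–3 attribute differences in pain and satisfaction to the procedure, but the primary objective is descriptive and the listed model contains neither diagnosis nor baseline pain

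*Protocol article*

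**What the plan says.** All references are to the protocol article.

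- **Primary objective.** The aim is descriptive: "To assess post-operative pain experiences by dental procedure type through 21 days post-procedure", together with satisfaction with pain management.
- **Hypotheses.** The lead sentence of Hypothesis 1 posits a difference across "dental procedure groupings after adjusting for pain management strategies and other complications". The follow-on sentence then asks "are their significant variations in pain intensity due to different treatments after adjusting for" a list of pain-management and complication variables. Hypotheses 2 and 3 repeat this form for pain interference and satisfaction.
- **Study outcome measures.** The covariate list begins "Other covariates are *Baseline pain intensity, Patient demographic* variables, *Type of procedure* (CDT") and continues with practitioner characteristics and the practitioner's expectation of pain. Diagnosis is not in it.
- **Instruments for data collection.** The case report forms hold "patient information (patient demographics, diagnoses and procedures, pain levels, pain management plan, and complications) at Days 0 & 21". Table 2 also lists diagnoses among the patient items.
- **Statistical analysis.** The aim is stated as modelling a differential treatment effect of the CDT grouping. "Models will include time, treatment type, age, gender, race/ethnicity, medications, and no medication methods as fixed effects", and "dentist and Network regions will be included as random effects in the models". The same section calls the relative risk a measure of association. Both it and the Limitation section acknowledge confounding and undertake to adjust for potential confounders, without naming any.

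**The concern.** The document frames its main comparison in two ways that do not agree. The objective can be met by describing what patients report after each type of procedure. The follow-on sentences in the hypotheses, and the treatment-effect wording in the analysis section, ask for the part of the difference that the procedure itself produces.

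The second question needs control of whatever led the patient to that procedure. The eligibility section names endodontic, periodontal, oral surgery and implant procedures, which serve different disease areas. The condition being treated is therefore an obvious candidate for a variable that affects pain and differs between groups, which is how the document itself defines a confounder. It is due to be recorded but has no place in the named analysis.

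At stake is the conclusion the study may draw. A contrast between procedure groups is a valid description of the patients in them. As a statement about what a procedure does, it would mix the procedure with the condition that led to it.

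**Working it through.** **Step 1: set the adjustment sets side by side.**

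| Place | Diagnosis | Baseline pain |
|---|---|---|
| Hypotheses 1–3, adjustment set | no | no |
| Study outcome measures, covariates | no | yes |
| Statistical analysis, listed fixed effects | no | no |
| Collected | yes, case report form | yes, before the procedure |

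The clinical adjusters that are named (medications, non-medication methods, complications) arise with or after the procedure, so they cannot stand in for a pre-existing condition. Age, gender and race/ethnicity do not identify the condition. The random effects handle clustering by dentist and region and do not record why a given patient had a given procedure.

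**Step 2: is there a stated figure to reproduce?** None bears on confounding. The sample-size section gives 3147 × (1 − 0.40) = 1888.2, which agrees with its 1888. It sizes the study for a 20% reduction, a ratio of 0.80, or 1/0.80 = 1.25 when inverted.

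**Step 3: illustrate what omission could do.** Every input here is assumed; the document supplies none. Suppose the procedure has no effect. One type of diagnosis multiplies mean pain by *k* and has shares *p1* and *p0* in two procedure groups. A log-link model that omits it shows

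apparent ratio = [1 + *p1*(*k* − 1)] / [1 + *p0*(*k* − 1)].

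| Shares *p1* v *p0* | *k* = 1.25 | *k* = 1.5 | *k* = 2 |
|---|---|---|---|
| 60% v 40% | 1.05 | 1.08 | 1.14 |
| 80% v 20% | 1.14 | 1.27 | 1.50 |
| 95% v 5% | 1.22 | 1.44 | 1.86 |

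For example, 80% v 20% with *k* = 1.5 gives 1.40/1.10 = 1.27. An intermediate case, 60% v 20% with *k* = 1.5, gives 1.30/1.10 = 1.18; inverted this is 0.846, about a 15% reduction. Some assumed combinations reach 1.25 and many do not.

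**Step 4: what adjustment would cost.** With two equal groups and the symmetric shares above, the correlation between diagnosis and procedure is *r* = *p1* − *p0*. The variance inflation for the procedure term is 1/(1 − *r*²).

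- 60% v 40%: *r* = 0.2, inflation 1.04, effective N 1888 × 0.96 ≈ 1812.
- 80% v 20%: *r* = 0.6, inflation 1.56, effective N 1888 × 0.64 ≈ 1208.
- 95% v 5%: *r* = 0.9, inflation 5.26, effective N 1888 × 0.19 ≈ 359.

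The more closely diagnosis determines procedure, the larger the possible bias and the less an adjusted contrast can tell us. Adding a covariate therefore cannot by itself rescue the causal wording.

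**The case against.** The strongest reply is that the study is descriptive and the causal phrase is loose drafting. The primary objective, the lead sentence of each hypothesis and the measure-of-association wording all point that way. For descriptive estimates by procedure, leaving diagnosis out is no error. This stands, and it is why rewording is the main remedy. It does not dispose of the point, because the causal form appears in all three hypotheses and is echoed in the analysis section.

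A second reply is that the article undertakes to adjust for potential confounders, and that its fixed-effect list is evidently incomplete: baseline pain and expected pain are declared covariates, and complications are in the hypotheses, yet none is in the list. A fuller plan may name diagnosis. That softens the point. But every adjustment set the article does print omits diagnosis, and an unnamed set cannot support a named causal claim.

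Third, no sentence in the article says that diagnosis fixes the procedure, and the CDT groupings used for analysis are not defined in it. That is correct. The premise is general reasoning from the range of procedures in the eligibility section.

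A reader might go further and infer that the study will report disease differences as procedure effects, or that the bias is about as large as the 20% difference it is sized for. The documents support neither. They give no diagnosis shares and no pain ratios, and nowhere do they say that a procedure causes pain.

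**Conclusion.** The point holds in a limited form. Hypotheses 1–3 and the treatment-effect wording go beyond the descriptive primary objective, and the listed model cannot carry the extra claim: the cohort is non-randomised, diagnosis is in no named adjustment set, and baseline pain is missing from the listed fixed effects. The general undertaking on confounders does not resolve this.

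The size of any bias cannot be derived from the document. The ratios of 1.05 to 1.86 rest wholly on assumed shares and pain ratios and on omitting baseline pain as well; they show only that the bias could range from trivial to larger than the design difference. The flaw limits what may be concluded. It does not impair the data or the by-procedure description.

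**What to change.** 1. Reword Hypotheses 1–3, and the treatment-effect sentence in Statistical analysis, as differences between patients undergoing each procedure type, in line with the primary objective. State that no causal conclusion about procedures will be drawn. This costs only a wording change.
2. As a supportive analysis only, report procedure contrasts with and without a recoded diagnosis category from the Day 0 case report form together with baseline pain. Restrict each contrast to diagnosis categories that occur in both procedure groups compared. This assumes diagnosis is entered at Day 0; the article gives Days 0 and 21 for the forms without saying which items fall on which day.

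The second step uses data already planned, at the cost of recoding one variable. Its downside is wider intervals, as the inflation factors above illustrate. Where two procedure groups share no diagnosis category, the contrast can only be reported descriptively.
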